### Study intervention

#### Experimental group: exercise training

The MT program will be conducted for 6 months, twice a week in 60 min sessions. Sessions will be divided in warm-up (10 min, including slow walk, postural and mobility exercises for general activation, and stretching exercises), specific training (35–45 min, including balance/coordination training, strength and aerobic exercises) and cool down (5 min with breathing and stretching exercises for the main worked joints and muscles) following the main guidelines recommended by the American College of Sports Medicine [43] and the WHO [44] (Table 3).

**Table 3 Tab3:** Exercise intervention plan for “Body & Brain” study

Warm-up	Balance & Coordination		Strength		Aerobic Resistance	Stretching & Cool down
General activation, joint mobilization, stretching exercises	Static and dynamic balance; coordination exercises		Strength exercises involving mainly major upper and lower body muscle groups		Low impact aerobic exercises involving walking, stationary march and dance	Lower body and upper body stretch, breathing exercises
e.g. slow walk, mobility exercises for the shoulders, trunk, hip, and ankles as rotations, flexion/extension and adduction/abduction	e.g. one leg stand, tandem walk, sideways walk, heel-to-toe walk, step over objects as cones, hoops and huddlers, exercises with balance pads, shift weight from foot to foot, turning and changing direction		e.g. biceps arm curl, triceps extension, adapted planks, seated row, chest press, squats, knee extension, hip extension, toe raises, standing leg curl		e.g. stationary marching, walking, simple step-based choreographic movements - exercises will start with only lower limbs and as needed will include upper limbs	e.g. back and chest stretch, quadriceps and hamstrings stretch, diaphragmatic breathing
**1st & 2nd months**						
10 min	15 min	2–3 exercises	15 min	4 exercises	10 min (5 + 5)	5 min
	Dynamic balance		2 × 10–12 reps		60–65% HRmax	
**3rd month**						
10 min	15 min	2–3 exercises	15 min	4–6 exercises	10 + 5 min	5 min
	Dynamic balance and coordination		2 × 10–12 reps		65–75% HRmax	
**4th month**						
10 min	10 min	2–3 exercises	15 min	4–6 exercises	10 + 10 min	5 min
	Dynamic balance and coordination		2 × 8–10 reps		65–75% HRmax	
**5th and 6th months**						
10 min	10 min	2–3 exercises	15 min	4–6 exercises	10 + 10 min	5 min
	Dynamic balance and coordination		2 × 8–10 reps		65–80% HRmax	

HRmax *Maximum heart rate,* min *Minutes,* reps *Repetitions*

Well-designed, routine, simple, enjoyable and functional exercises will be preferred. A 1 month adaptation period, before the training program, will be implemented with the main purpose of promoting familiarization with exercises and socialization between participants [45]. New exercises should be introduced based only as a progression of previous well-known exercises. In the adaptation period the focus will be in learning the movements keeping a low intensity, of 40 to 50% of HRmax in the aerobic exercises and 1 set of 12 to 15 slow repetitions for the strength exercises.

Exercise prescription, implementation and evaluation will be performed by specialized exercise professionals. Furthermore, prior to the program implementation, those professionals will receive specific training concerning dementia (clinical features, signs and symptoms), challenging behaviors, communication strategies, and other related topics (e.g., safety issues) [46].

Sessions, involving 5 to 12 participants will be held in appropriate spaces and in a safe and calm environment to limit distractions and maximize the individuals’ participation [46]. Sessions are going to be scheduled in the late morning or in early afternoon period, and the sports equipment encompasses chairs, ground markers, strings, elastic resistance bands, dumbbells, hurdles, balance pads, balls, and steps. Whenever possible, sessions will be accompanied by music, particularly during the aerobic part, in order to confer appropriate exercises intensity and enthusiasm [45].

Balance exercises will gradually reduce the base of support and/or reduced sensory input as well as include dynamic movements that perturb the center of gravity. These progressions will occur when participants reach the time limit without losing control of the body. Also, focus on some easy coordination exercises and conscious control of the body will be performed.

Four to 6 multi-joint strength exercises involving major muscle groups will be included in each session. The number of repetitions will decrease from 10 to 12 to 8–10 with increasing load that could be lifted correctly to volitional fatigue. A rest period of 1′30’-2″ will be completed between each set.

Aerobic endurance will be attained with low impact exercises at 60–65% of HRMax implemented in two 5-min periods. Intensity will increase progressively with increasing duration and HR until reaching 2 periods of 10 continuous minutes of exercise at 75 to 80% of HRmax. Sessions will be monitored using heart rate monitors [47], and whenever possible, the Modified Borg Scale of Perceived Exertion will be applied.

Exercise professionals will registry adverse events (such as pain or fatigue) and number of falls during exercise sessions to provide information on safety of the MT program. Finally, attendance to sessions will be recorded and reasons for absences the will be catalogued [48].

Although this is not a dyadic intervention, caregivers will be included in each session as class members, but focus will be directed to individuals diagnosed with dementia. Along with the novelty of this strategy, this approach will facilitate dementia patients’ participation once their transportation, motivation, and involvement are dependent of their caregivers [49, 50]. Additionally, caregivers’ participation will also be determinant to deal with behavioral and psychological symptoms of dementia patients [46].

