### Trial design

This study is a multicenter quasi-experimental controlled trial with a parallel design, that will be conducted in a wide-ranging public and private settings (e.g., daycare centers and local community centers) in the Porto metropolitan area, Portugal. Participants will be recruited from community programs, daycare centers, psychiatric hospitals and clinics (i.e., outpatients followed within psychiatry or neurology specialists), Alzheimer’s and caregivers’ associations, municipalities, local journals, and social media. Advertisements will be made via phone calls, emails, informative flyers and presential and online meetings. In order to motivate and clarify concerns about the exercise sessions, a short MT session will be provided to exemplify and illustrate a typical session for individuals with dementia.

Eligible participants and caregivers will receive a complete explanation of the study purposes, risks and procedures. Following the best ethical procedures, informed consent will be obtained from interested dementia participants and from their main caregivers/legal representatives/significant person. After agreeing to participate and according to personal availability, participants will be allocated into a 6-month MT intervention (IG) or into a social activity group (CG) (see Fig. 1). All CG participants will be offered the possibility to participate in an exercise program after the end of the study cycle.

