#### Sample size

Sample size was estimated based on ANCOVA for the analysis of the differences [41]. To detect an adjusted 1 point (SD = 2.1) difference in SPPB after intervention between IG and CG with 80% power and an alpha level of 0.05, a total of 110 participants (55 participants per group) will be needed, already accounting for an estimated dropout of 25%. Sample size calculation was performed using G*Power 3.1.3 (Universität Düsseldorf, Düsseldorf, Germany) [42].

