#### Control group: social activity

Participants in the control group will receive monthly sessions regarding physical activity and health-related topics as a complement to standard care. No specific exercise intervention will be conducted for this group. Due to ethical reasons, there will be no limit on co-interventions during the trial. Pharmacological, medical or other types of treatments may be initiated, continued or discontinued independently of research team approval. However, participants who eventually are going to participate in further co-interventions will be signalized, and information on type and duration will be collected and considered as covariates in statistical procedures. Participants are going to be contacted with a regular basis via phone calls to assure retention and motivation.

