### Statistical analysis plan

Descriptive statistics will be expressed as mean and standard deviation (SD) or as median and interquartile range (IQR) for continuous variables. Categorical variables will be expressed as frequency and percentages. Normal distribution will be analyzed by the Kolmogorov-Smirnov test with Lilliefors’ (K–S) significance correction and normal probability plots. Statistical comparisons at baseline characteristics will be performed using t-test or Mann–Whitney U-test for continuous variables and Chi-squared test or Fisher’s test for categorical variables.

Age, gender, level of education, dementia type/stage, and other variables will be considered as potential confounders and adjustments will be performed in accordance to detect differences between experimental and control group.

The primary effect parameter will be the difference in the SPPB and ADAS-Cog tests between the experimental and control groups, considering the two different moments of evaluation (baseline and after 6-month of intervention). An analysis of variance (ANOVA) test with repeated measures adjusted for potential confounders will be performed for the intervention-related effects. When a significant F value is obtained, Bonferroni post hoc procedures will be used to evaluate pairwise differences. Additionally, mixed effects models will be performed in order to identify potential predictive factor associated with the changes in primary and secondary outcomes from baseline, post-intervention and over the 3-months detraining period.

A multivariable regression analysis will be performed in order to explore the association between cardiovascular and blood-markers, and cognition.

Statistical analyses will be conducted with the SPSS IBM Statistical Software version 25.0 (SPSS, Inc., Chicago, IL) for Windows with a significance level of *p* < 0.05.

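### Exercise is delivered in classes, but neither the sample size nor the stated primary analysis allows for correlation within class; if there is any, the real type I error exceeds 5%

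*Protocol article*

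**What the plan says.** All references are to the protocol article; no separate analysis plan is at hand.

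- **Delivery, exercise arm** (Study intervention, Experimental group): "Sessions, involving 5 to 12 participants will be held in appropriate spaces". The same section adds that "caregivers will be included in each session as class members".
- **Delivery, control arm** (Control group: social activity): "Participants in the control group will receive monthly sessions regarding physical activity and health-related topics". Whether these sessions are held in groups, and of what size, is not stated.
- **Setting and allocation** (Trial design): "This study is a multicenter quasi-experimental controlled trial with a parallel design". Allocation is individual: "according to personal availability, participants will be allocated into a 6-month MT intervention (IG) or into a social activity group (CG").
- **Sample size**: "To detect an adjusted 1 point (SD = 2.1) difference in SPPB after intervention between IG and CG". Power is set at 80% and alpha at 0.05, and the result is 110 in total (55 per group) with 25% dropout included. No ICC or design effect is mentioned.
- **Primary analysis** (Statistical analysis plan): "An analysis of variance (ANOVA) test with repeated measures adjusted for potential confounders will be performed for the intervention-related effects". The named adjustment variables are age, gender, education and dementia type or stage, plus unspecified others. Mixed models are planned in addition, to look for predictors of change, and no random effects are listed.

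**The concern.** Patients in one class share a venue, a peer group and the session plan in Table 3. The adaptation month is partly meant to encourage socialising. Some correlation of response within class is therefore plausible. An analysis that counts each patient as independent then credits the exercise arm with more information than it holds. The standard error of the group difference is too small, and the p-values for SPPB and ADAS-Cog are too small with it.

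Adding covariates to the ANOVA cannot repair this. Exercise classes exist only in the intervention arm, so a full set of class indicators is collinear with group. A random class effect or cluster-robust errors are needed.

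**Working it through.** **1. Does the plan's own figure contain a clustering allowance?**

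Inputs from the Sample size section: difference 1, SD 2.1, power 80%, alpha 0.05, dropout 25%.

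- Two-sided, no covariate gain: n = 2(1.960 + 0.842)² × 2.1² / 1² = 69.2, so 70 per arm. After dropout 70/0.75 = 93.3, so 94 per arm (188 in total), not 110.
- With an unstated baseline–outcome correlation of 0.64: 69.2 × (1 − 0.64²) = 40.9, so 41 per arm. After dropout 41/0.75 = 54.7, so 55 per arm, or 110.
- One-sided with no dropout: 2(1.645 + 0.842)² × 2.1² = 54.5, so 55 per arm, or 110.

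The figure cannot be reproduced from the stated inputs alone. Neither route that reaches 110 leaves room for a design effect.

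**2. Formulas for the effect of ignoring class**

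Let m be the number of analysed patients per class. The ICC is that of the change or baseline-adjusted outcome.

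- Design effect in the exercise arm: DE = 1 + (m − 1) × ICC.
- Only that arm clustered, equal arms: the variance of the difference is multiplied by V = (1 + DE)/2.
- Real two-sided alpha = 2 × [1 − Φ(1.96/√V)].

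**3. Choice of m**

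- 5 and 12 are the stated limits; 8.5 is their midpoint.
- With 25% dropout, about 41 of 55 are analysed, so a class of 8.5 shrinks to 8.5 × 41/55 = 6.3.
- If the 5 to 12 counts caregivers and half are patients (an assumption), the midpoint is 4.25, or 4.25 × 41/55 = 3.2 after dropout.

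**4. Results (ICC assumed throughout)**

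| m | ICC 0 | ICC 0.01 | ICC 0.05 | ICC 0.10 |
|---|---|---|---|---|
| 3.2 | 5.0% | 5.1% | 5.6% | 6.3% |
| 4.25 | 5.0% | 5.2% | 5.9% | 6.9% |
| 5 | 5.0% | 5.2% | 6.2% | 7.4% |
| 6.3 | 5.0% | 5.3% | 6.6% | 8.1% |
| 8.5 | 5.0% | 5.4% | 7.2% | 9.5% |
| 12 | 5.0% | 5.6% | 8.3% | 11.5% |

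Example, m = 8.5 and ICC 0.05: DE = 1 + 7.5 × 0.05 = 1.375; V = 2.375/2 = 1.1875; 1.96/√1.1875 = 1.799; alpha = 7.2%.

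**5. Check by simulation**

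An unadjusted t-test with 41 per arm, 40,000 runs and nominal class size 8 rejected in 5.2%, 7.0% and 8.6% of runs at ICC 0.01, 0.05 and 0.10. The formula gives 5.4%, 7.1% and 9.2% at m = 8. The simulated values are slightly lower, in part because 41 patients in six classes average 6.8 per class.

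**6. Centres**

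In a simulation with five centres, each holding both arms in equal numbers, ignoring centre gave 4.5% at ICC 0.05 and 4.1% at ICC 0.10. That is conservative.

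**The case against.** The strongest reply is that the excess depends wholly on an ICC that the documents do not give. It is nil at ICC 0 and slight at 0.01. The primary contrast compares change from baseline to six months, so stable differences between classes cancel, and only correlation of the change matters. Parts of the training are individually progressed, which may weaken any class effect. Caregivers in the class and dropout both make the patient clusters smaller than the stated 5 to 12. All of this stands, and it is why the point is conditional.

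A further reply is that the article is condensed, leaves room for other covariates and already plans mixed models. This stands only in part. The article names the primary test, that test has no class term, and further covariates cannot supply one. The mixed models serve a different purpose.

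A reader might infer three stronger points that the documents do not support:

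- **Several centres by themselves make standard errors too small.** They do not if centres hold both arms. Error is inflated only if centre and arm overlap, which allocation by availability permits but the text does not state.
- **Clustering in both arms, with a much larger type I error.** The format of the control sessions is not given.
- **A specific loss of power.** Any such figure needs a baseline correlation that the Sample size section does not state.

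**Conclusion.** The point holds in conditional form. The plan delivers exercise in classes, sizes the trial without a clustering allowance, and tests both primary outcomes with a model that treats participants as independent. Whenever the within-class ICC of change is above 0, that test is anti-conservative. The top of the range, 11.5%, needs 12 analysed patients per class and an ICC of 0.10; the more moderate inputs at ICC 0.05 add roughly one to two percentage points to the nominal 5%. These figures assume a two-sided test, equal arms and independent controls. The direction of the effect is certain if the ICC is positive; its size is not known from the documents.

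**What to change.** 1. Record an exercise-class identifier and a centre identifier for each participant. Recruitment was still open when the article appeared, so this can be done as participants enter.
2. Make the primary comparison for SPPB and for ADAS-Cog a mixed model with a random class effect in the exercise arm only. Each control forms its own cluster unless the control sessions turn out to be grouped. Use small-sample degrees of freedom.
3. Report the estimated ICC and a table of centre by group. If a centre supplies only one arm, no model term can separate centre from treatment, and the table shows readers where that occurs.
4. State in the Sample size section that 110 assumes no clustering, and whether the 5 to 12 per session counts patients only.

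The cost is analysis wording and two identifiers, since mixed models are already planned. Confidence intervals will be wider. With 55 patients there would be about 5 (55/12) to 11 (55/5) classes, fewer if caregivers do not count in the class size and classes are small in number, so the class variance will be imprecise. In the limiting case where the degrees of freedom fall to the number of classes minus one (4 to 10), the critical value would be 2.78 to 2.23 in place of 1.96.

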**Fig. 1 Fig1:**
[figure not shown]
Study Flow Diagram

Participants will be assessed at baseline, after 6-month of intervention, and 3-month follow-up after the end of intervention (Table 1). At baseline, sociodemographic (e.g., age and years of formal education), general clinical data (e.g., presence of comorbidities, pharmacological treatment, and falls) will be collected through a structured questionnaire, and dementia rating severity evaluation will be performed trough the Clinical Dementia Rating (CDR) outcome measurement [38]. During baseline assessments, participants will not be informed regarding to which group they belong. Data collection will be performed by well-trained and experienced researchers.

**Table 1 Tab1:** Description of methods and/or instruments to evaluate IwD and/or their caregivers/significant person/proxy decision-maker

	Domain	Measure	Data from	
			IwD	Caregiver
**Screening**	Informed Consent		X	X
	Anamnesis (sociodemographic and general clinical data)			X
	Clinical Dementia Rating		X	X
**Primary**^**a**^	Cognition			
	Cognitive Function	ADAS-Cog	X	
	Physical Fitness			
	Lower Limb Function	SPBB	X	
**Secondary**^**a**^	Cognition			
	Cognitive Function	MMSE	X	
		TMT		
	Physical Fitness			
	Cardiorespiratory Capacity	Modified Bruce Treadmill Test	X	
	Physical Fitness	SFT	X	
	Static Balance	One Leg Balance Test	X	
	Handgrip Strength	Handgrip Dynamometer	X	
	Body Composition and Anthropometry			
	Body Mass	DXA (Hologic QDR 4500, Explorer model, version 12.4)	X	
	Total Fat-free Mass			
	Fat Mass			
	Appendicular Skeletal Mass Index			
	Weight	Weighting Scale	X	
	Height	Stadiometer	X	
	Waist and Hip Circumferences	Measuring Tape	X	
	Quality of Life and ADL’s Functionality			
	Basic and instrumental ADL	Lawton & Brody IADL Scale		X
		Barthel Index		
	Quality of Life	QoL-AD	X	X
	Behavioral and Psychological Symptoms of Dementia			
	Neuropsychiatric Symptoms and Caregiver Distress	NPI		X
	Caregiver Burden			
	Caregiver Well-being and Subjective Burden	CarerQol-7D		X
		CarerQol-Vas		
	Blood-based Biomarkers and Hemodynamics			
	Systolic and Diastolic Blood Pressure	Digital Sphygmomanometer	X	
	Arterial Stiffness	Pulse Wave Velocity (SphygmoCor, AtCor Medical, Australia)	X	
	TG	Concentration in blood plasma	X	
	TC			
	LDL-C			
	HDL-C			
	HbA1c	HPLC		
	BDNF	ELISA	X	
	VEGF			
	CRP			
	sICAM-1			
	sVCAM-1			
	MMP-9			
	IL-6, IL-8, IL-10			
	TNF-alfa	CLIA	X	
	IGF-1			
**Confounders**^**a**^	Daily Physical Activity			

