	Physical Activity Levels	Accelerometer-based activity monitors *GT9X+ Link* (ActiGraph)	X	

^a^*T0* Baseline, *T1* After 6-month intervention, *T2* 3-month follow-up

The same evaluator will be responsible to perform the same procedures along the three assessment periods, which will be subdivided in five separate moments (Table 2). The exercise professional who is going to provide the MT sessions will not be involved in any data collection.

**Table 2 Tab2:** Schedule for the different primary and secondary and outcomes, screening, and confounder evaluations of each assessment moment per evaluator

*Assessment moments per evaluator*	Prior to Assessment (only at baseline)	1st Cognition & Functionality^**a**^	2nd Cognition, QoL & Physical Fitness^**a**^	3rd Physical Activity Level^**a**^	4th ADL, QoL, BPSD & Caregiver Burden^**a**^	5th Body Composition, Cardiorespiratory Fitness, Hemodynamics & Blood-based Biomarkers^**a**^
***Evaluator 1***	CDR	MMSE TMT	ADAS-Cog QoL-AD patient		QoL-AD caregiver Carer-QoL NPI Barthel Index Lawton & Brody IADL Scale	
***Evaluator 2***		SPPB Handgrip strength	SFT One Leg Balance Test	7-day accelerometer-based monitor		
***Evaluator 3***	Informed Consent and anamnesis (sociodemographic and general clinical data)					VO2 Peak Consumption Anthropometry DXA Body Composition Blood Pressure Arterial Stiffness
***Laboratory***						Blood Analysis

^a^*T0* Baseline, *T1* After 6-month intervention, *T2* 3-month follow-up

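### As described, on-study falls and adverse events are recorded only in the exercise arm, so the plan can describe in-session safety but cannot compare safety between arms

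*Protocol article*

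**What the plan says.** Four places in the protocol article bear on this.

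- **Experimental group: exercise training.** "Exercise professionals will registry adverse events (such as pain or fatigue) and number of falls during exercise sessions to provide information on safety" of the programme. The next sentence adds an attendance log with the causes of missed sessions. On exposure: "The MT program will be conducted for 6 months, twice a week in 60 min sessions".
- **Control group: social activity.** "No specific exercise intervention will be conducted for this group". The section describes monthly information sessions, the logging of co-interventions, and calls: "Participants are going to be contacted with a regular basis via phone calls to assure retention and motivation". It does not mention recording events.
- **Trial design, text.** At baseline, "general clinical data (e.g., presence of comorbidities, pharmacological treatment, and falls) will be collected through a structured questionnaire". This covers all participants.
- **Trial design, Tables 1 and 2.** The questionnaire (anamnesis) is a screening item in Table 1, and Table 2 places it before the assessments, at baseline only. The measures for T0, T1 and T2 are itemised; none is a fall, injury, hospital-admission or adverse-event item. The text before Table 2 also says: "The exercise professional who is going to provide the MT sessions will not be involved in any data collection".

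Safety is not among the declared purposes, the primary or secondary outcomes, or the analyses in the Statistical analysis plan section.

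**The concern.** The recording rule is specific. It names who records, what is recorded, in which setting and for what purpose, and the setting exists in one arm only. Followed as written, ascertainment is one-sided: the exercise arm gets an event count and the control arm gets none.

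This matters for two reasons. First, pain and fatigue, the article's own examples of adverse events, also arise from background illness in older people with dementia. Without a control count there is nothing to set them against. Second, the physical primary outcome measures balance, gait and lower-limb strength, so falls in daily life are a natural consequence of what is trained, for better or worse. They would not be counted in either arm. The Discussion hopes to see exercise prescribed more widely in this population, and in-class counts from one arm are a thin safety basis for that.

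**Working it through.** The plan gives no safety figure to reproduce. The check traces where events could be captured, then sizes what the described recording can and cannot show.

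**1. Capture by arm and period, as described**

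| Period | Exercise arm | Control arm |
|---|---|---|
| Baseline | Falls item in questionnaire | Same |
| 6 months, in session | Events and falls recorded by instructors | No exercise sessions; no event recording described |
| 6 months, outside sessions | Nothing designed for it; causes of absence may reveal some events | Nothing described; calls are for retention and motivation |
| T1 assessment | No event item | No event item |
| 3-month detraining | No sessions, nothing described | Nothing described |
| T2 assessment | No event item | No event item |

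The sentence can be parsed so that the in-session limit applies to falls alone. The recorder is still the class instructor, so the control column does not change.

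**2. Observation window**

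Inputs: two 60-minute sessions a week for 6 months (taken as 26 weeks), then 3 months of follow-up (39 weeks in all).

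- Session hours per participant: 26 × 2 × 1 h = 52 h.
- Share of the week during training: 2 / 168 = 1.2%.
- Share of the whole study: 52 / (39 × 168) = 52 / 6,552 = 0.8%.
- Control arm: 0 h.

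These are shares of clock time, not estimates of the share of events missed.

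**3. What in-session recording can show**

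Inputs: 55 per group and 25% dropout, from the Sample size section. 55 × 0.75 = 41.25, taken as 41.

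- Full attendance, no dropout: 55 × 52 = 2,860 participant-sessions.
- After dropout, if dropouts contribute nothing: 41 × 52 = 2,132.
- Rule of three for zero observed falls, upper 95% bound = 3 / sessions: 3 / 2,860 = 1.0 per 1,000, and 3 / 2,132 = 1.4 per 1,000.

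The bound treats sessions as independent. Missed sessions, or falls clustered in a few participants, would widen it.

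**4. What a symmetric question at T1 and T2 would add**

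- Person-months per arm with full retention: 55 × (6 + 3) = 495.
- After dropout, if dropouts contribute nothing: 41 × 9 = 369.

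The described plan collects no control-arm events over any of this time.

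**The case against.** The case against has force, and several stronger readings that a reader might infer do not hold.

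- **That the safety purpose cannot be met.** The stated purpose is only to inform on the safety of the programme. In-session counts do that in part (step 3). Safety is not a declared aim or outcome, and no between-arm comparison is promised.
- **That about 99% of at-risk time, or of events, goes unseen.** The 1.2% is clock time. It counts sleep, treats all hours as equally risky, and ignores that pain or fatigue may be reported at the next class. It cannot be turned into a number of missed events.
- **That every out-of-class event in the exercise arm is lost.** An injury or admission that keeps someone from a twice-weekly class may appear among the logged causes of absence. This source is incidental and incomplete, but it exists.
- **That the article contradicts itself on who collects data.** The sentence excluding instructors introduces the evaluator schedule and can be read as covering outcome assessments only. It needs a clarifying word; it is not proof of an error.
- **That the telephone calls reach both arms.** They are described in the control-group section only.
- **That no other event procedure exists.** This is a journal article, and a fuller protocol may hold trial-wide procedures. Silence alone would be no finding.

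The last objection does not dispose of the point. The article goes beyond silence: it states a recording rule tied to one arm, dates the falls questionnaire to baseline, and itemises the later assessments without an event item.

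**Conclusion.** The point holds in limited form. As described, on-study falls and adverse events are registered only by exercise professionals in the exercise arm, with falls counted in session. The plan can describe in-session safety, with an upper bound of about 1.0 to 1.4 falls per 1,000 participant-sessions if none occurs. It cannot compare falls or adverse events between arms, and it would largely miss delayed, out-of-class and detraining-period events.

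This rests on reading the article as printed, on 26 weeks of twice-weekly sessions, and on full attendance for the bound. If a fuller protocol already collects events in both arms, what remains is to say so in the published text. The point does not touch the SPPB or ADAS-Cog analyses. It is a change that should be made, because the visits needed for it are already planned.

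**What to change.** 1. At T1 and T2, in the caregiver interview that Table 2 already schedules (the fourth assessment moment), repeat the baseline falls item. Add identical short questions in both arms on injury, hospital admission and adverse events since the last visit.
2. State whether the regular telephone calls go to both arms. If they do, ask the same questions there, which shortens the recall period.
3. Report these events descriptively by arm, per person-month. Report in-session events separately, as exercise-arm-only data per participant-session.
4. Clarify that the exclusion of exercise professionals from data collection refers to outcome assessments, since they also record events and attendance.

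**Cost.** A few questions at visits that already take place in both arms. Caregiver recall over 6 months (to T1) and 3 months (to T2) is imperfect. It may also differ by arm, because exercise-arm caregivers attend the classes and know the allocation. Allocation follows personal availability and is not random, so a difference between arms should be described and not read as caused by the programme.
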